## **8.5 Statistical methods**

### **8.5.1 General statistical methods**

Subjects will be used as their own reference comparing pre- (baseline) and post-treatment.

Descriptive statistics will be used for description of the frequency and nature of the adverse events. The number and frequency of all adverse events and the adverse events considered possibly or probably related to study will be listed by dose, cumulative dose, body system and by coded term. In addition, the number of subjects experiencing an adverse event will be listed by dose, cumulative dose, body system and by coded term.

Quantitative (incl. biochemical, hematology, muscle strength) parameters will be expressed as mean  $\pm$  SD, median, minimum and maximum per visit.

Pharmacokinetics and dose response relations will be evaluated using population and sparse data analysis.

The analyses will be performed according to the Statistical Analyses Plan that will be available before the database is locked. Deviations from the Statistical Analyses Plan will be justified in the study report.

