Patients will receive one subcutaneous treatment of PRO051 per week for a period of five weeks (i.e. five injections in total). This number of injections was considered sufficient to establish the MTD and a dose level to investigate in future studies prior to embarking on trials with longer treatment duration. After the five weeks of treatment period, the patients will continue with follow up visits till 13 weeks after the last treatment.

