## 3.2 Study treatments

### 3.2.1 Treatments administered

Successive cohorts of 3-6 patients will receive PRO051 by subcutaneous injection on day 1, 8, 15, 22 and 29. The number of injection sites per administration depends on the total dose to be administered but will not exceed two injection sites.

Patients in the first group will receive 0.5 mg/kg, in the second group maximally 2 mg/kg, in the third group maximally 6 mg/kg and in the fourth group maximally 10 mg/kg.

Dose escalation will only take place after review by the investigators and the medical responsible person of the sponsor as described in section 3.1.

If review of the safety data raises concerns about the next dose level to be administered, the dose level may be adjusted downwards. If this occurs, the IEC/IRB and regulatory authorities if applicable will be notified of changes in planned dose levels.

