### **3.3.2      Follow-up period during study**

Follow-up visits take place on Days 36, 43, 57, 78, 99 and 120.

Assessments as indicated in the Schedule of assessments (Appendix 2: Table 4) will be made during each of these follow-up assessments.

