## 7.2 Reporting of adverse events

At each evaluation, the investigator will determine whether any adverse events have occurred. If any adverse events have occurred, they will be recorded on the adverse event report pages of the CRF. If known, the diagnosis should be recorded, in preference to the listing of individual signs and symptoms.

Any adverse event experienced by the subject from the time of signing the informed consent until 30 days after the end of the study will be recorded on the CRF.

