#### **8.5.5.4      Safety analysis**

- Adverse events (AEs) will be coded and presented using MedDRA. The overall incidence, the incidence of possibly or probably related as well as the incidence of serious adverse events will be summarized per body system in tables. An adverse event that occurred during the study medication period or at follow-up will only be counted as an adverse event if it was either not present at baseline or it was present at baseline but increased in severity during the treatment period.
- Vital Signs (supine blood pressure and heart rate): Descriptive statistics (n, mean, standard deviation, median, minimum, and maximum) will be provided on blood pressure along with heart rate at baseline and all post-dose assessments.
- Hematology, urinalysis and clinical chemistry parameters: Descriptive statistics (n, mean, standard deviation, median, minimum, and maximum) will be provided on values at baseline and all post-dose assessments. Descriptive statistics will be calculated on the change from baseline measurements. Out-of-normal-range values will be indicated for each parameter. The change in out-of-normal-range values after administration and at follow up versus baseline will be summarized by means of shift-tables.
- ECG: Descriptive statistics (frequency, mean, standard deviation, median, minimum, and maximum) on ECG parameters will be provided at baseline and all post-baseline

assessments. Changes from baseline measurements will be calculated and descriptive statistics will be computed. Shift tables will also be provided to indicate changes in ECG parameters over time.

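### Adverse events listed by cumulative dose carry no observation time, although the fifth level is observed for 91 days and each earlier one for 7

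*Protocol*

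**What the plan says.** Section 8.5.1 sets out two listings. For events, the sentence begins "The number and frequency of all adverse events and the adverse events considered possibly or probably related to study will be listed by dose, cumulative" (meaning the total dose received so far or in all), and its further keys are body system and coded term. For subjects, "the number of subjects experiencing an adverse event will be listed by dose, cumulative dose, body system and by coded term". Neither sentence mentions time at risk. Section 8.5.5.4 adds only incidence per body system.

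The schedule is fixed elsewhere. Section 3.2.1: "Successive cohorts of 3-6 patients will receive PRO051 by subcutaneous injection on day 1, 8, 15, 22 and 29". Section 3.3.2: "Follow-up visits take place on Days 36, 43, 57, 78, 99 and 120". Section 3.1 agrees that "the patients will continue with follow up visits till 13 weeks after the last treatment".

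Events in the long follow-up belong in the tables. Section 8.5.5.4 says "An adverse event that occurred during the study medication period or at follow-up will only be counted as an adverse event if" it is new or has worsened since baseline, so follow-up events qualify on the same terms as those in the treatment weeks. Section 7.2 collects for longer still: "Any adverse event experienced by the subject from the time of signing the informed consent until 30 days after the end of the study" is recorded.

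Sections 8.5.1 and 8.5.5 leave further detail to a statistical analysis plan, which is not at hand.

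**The concern.** Safety and tolerability at different dose levels is a stated objective (section 2), and accumulation is the protocol's own worry. Section 5.6.5.1 notes accumulation in liver and kidney, and the intermittent schedule in the extension is partly justified by organ burden. Cumulative dose is the axis on which a reader would look for accumulation toxicity.

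Weekly dosing gives one week at each of the first four cumulative doses. The fifth takes in the whole 13-week follow-up. A table of counts on that axis mixes cumulative dose with length of observation. There is no control group (section 3.1) in which the same background pattern could be seen. Ordinary childhood illness, or events after the muscle biopsies on day 43 and, in cohorts 2 to 4, day 78 (section 5.2.1), would collect at the highest level and could be taken for a drug effect.

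**Working it through.** **Inputs.** Dosing days 1, 8, 15, 22 and 29 (section 3.2.1); last study-period visit on day 120, window ±3 days (section 3.3.2, Table 4); recording to 30 days after end of study (section 7.2); maximum doses 0.5, 2, 6 and 10 mg/kg, three boys per cohort initially (section 3.1). The documents give no background event rate. I assume 0.05, 0.1 and 0.2 events per boy-week.

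**Step 1: the plan's own figure.** 120 − 29 = 91 days, and 91/7 = 13 weeks, as section 3.1 states.

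**Step 2: days at each cumulative dose.** Levels 1 to 4: 8 − 1 = 15 − 8 = 22 − 15 = 29 − 22 = 7 days each. Level 5: 91 days. Total 4 × 7 + 91 = 119.

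- Share at level 5: 91/119 = 76%. Ratio to any earlier level: 91/7 = 13.
- With the visit window, level 5 lasts 88 to 94 days, a ratio of 12.6 to 13.4.
- With the 30-day recording tail, and treatment not resumed, it lasts 121 days: 121/7 = 17.3 times, and 121/149 = 81% of the time.

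**Step 3: event counts, constant rate, no drug effect.** Expected events = boys × rate × weeks. For 12 boys at 0.1 per boy-week: 12 × 0.1 × 1 = 1.2 at each of levels 1 to 4, and 12 × 0.1 × 13 = 15.6 at level 5. The 13:1 ratio holds at any constant rate.

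**Step 4: boys with at least one event.** P = 1 − exp(−rate × weeks).

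| Assumed rate per boy-week | Levels 1–4 (1 week) | Level 5 (13 weeks) | Ratio |
|---|---|---|---|
| 0.05 | 5% | 48% | 9.8 |
| 0.1 | 10% | 73% | 7.6 |
| 0.2 | 18% | 93% | 5.1 |

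**Step 5: can the counts point the wrong way?** Suppose the rate is 0.3 per boy-week for the five weeks from the first dose and 0.1 afterwards. Each early level has 0.3 events per boy. Level 5 has 0.3 × 1 + 0.1 × 12 = 1.5. The count rises fivefold while the weekly rate falls from 0.30 to 1.5/13 = 0.12.

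**Step 6: pooling in mg/kg.** With three boys per cohort at the maximum doses, boy-days are 3 × 91 = 273 at totals of 2.5 and 50 mg/kg. At 10 and 30 mg/kg they are 273 + 21 = 294, because a cohort 4 boy passes through those totals at his first and third doses. Every other total has 21 or 42.

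**Step 7: with a time denominator.** Under the constant rate of step 3, events per boy-week are 1.2/12 = 0.1 at levels 1 to 4 and 15.6/156 = 0.1 at level 5. The false step is gone.

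**The case against.** **The assignment rule is not stated.** The artefact needs each event to be assigned to the cumulative dose reached at onset. If cumulative dose means each boy's final total, all completers have the same 119 days and the step disappears. This stands as a condition on the finding. It is the less natural reading: in the study period a completer's total is five times his weekly dose, so the axis would largely repeat dose, which the sentence lists separately. Withdrawals and individual dose adjustments would make it differ only at the margin.

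**This could be left to the analysis plan.** That plan may add person-time, and the word frequency is not defined in 8.5.1. But sections 8.5.5.1 and 8.5.5.2 use frequency as a count beside a percentage, and nothing points to a rate per unit time. The protocol itself chooses the cumulative-dose listing, so the point concerns something stated.

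**Recorded rates need not be constant.** Treatment weeks have an overnight stay of about 30 hours and a telephone call at 96 hours (section 3.3.1), while later visits are up to three weeks apart. Closer observation would raise early counts and may partly offset the step. The biopsies push the other way. This stands, and the size of the offset cannot be worked out from the documents.

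**Background events are partly filtered.** Related events are listed separately, and baseline events that did not worsen are excluded. This helps but does not remove the problem: relatedness is judged without a control group, and new intercurrent events in follow-up still count.

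**Nothing is decided on this table.** Escalation and the maximum tolerated dose rest on dose-limiting toxicity, reviewed after at least the first three doses (section 3.1, Table 2), and the synopsis says no formal analysis is planned. This is right and limits the weight of the point.

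**Conclusion.** The point holds, on condition that events are assigned to the cumulative dose reached at onset. Under a constant background rate, about 76% of post-dose events fall at the fifth level, 13 times the count at any earlier one. For boys with an event the excess is about 5-fold to 10-fold over the assumed rates. The direction does not depend on the rate chosen; the subject-level size does.

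A reader might infer three stronger things that the documents do not support.

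- That the table would show a smooth, steep rise with cumulative dose. Within a cohort it is one jump at the fifth dose; pooled in mg/kg it is spikes at 2.5, 10, 30 and 50.
- That the 13-fold figure describes boys affected. It applies to event counts only.
- That time beyond a week after the last dose is free of drug. Section 5.4 expects a terminal half-life of about 4 weeks and section 1.3.2 gives 27 days. At 27 days, 2^(−7/27) = 84% of the terminal-phase level remains after 7 days, so delayed toxicity there is plausible.

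This is worth correcting because the table invites a reading on accumulation that its counts cannot bear. It does not threaten the escalation rules.

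**What to change.** In section 8.5.1, state that an event is assigned to the cumulative dose reached at onset. Keep the counts of events and of subjects. Beside them give, for each cumulative-dose interval, the boy-weeks observed and the events per boy-week.

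Report the first 7 days after dose five as their own row, comparable with the four earlier weeks, and the remaining 91 − 7 = 84 days as a second row. Label that row post-treatment follow-up, not off-drug, because of the half-life.

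Use the same denominator in the extension, where intervals are again unequal. With eight weekly doses followed by four weeks without, the last dose of a cycle is followed by 5 weeks before the next dose, against 1 week after each of the others.

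The cost is a few lines of text and slightly more programming. Administrations are recorded on the CRF (section 3.2.6) and so are adverse events (section 7.2). The protocol does not list the fields of the adverse event page, so the presence of an onset date should be confirmed. The rates will be imprecise: a three-boy cohort gives only 3 boy-weeks at each of levels 1 to 4 against 39 at level 5. That is why the counts and boy-weeks should stay visible beside the rates.

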### **8.5.2 Interim analyses**

Not applicable.

### **8.5.3      Sample size justification**

The sample size has been chosen on scientific/medical grounds rather than on statistical grounds, because of the low prevalence of DMD subjects carrying a mutation correctable by PRO051.

### **8.5.4      Evaluability of data**

All subjects receiving at least one dose of study medication will be included in the safety analysis population.

All subjects receiving at least one dose of study medication, and in whom at least one effect parameter post baseline is available will be included in the ITT analysis population.

All subjects completing the protocol and in whom no major protocol violations have been noticed will be included in the per protocol population.

All subjects receiving at least one dose of study medication, and in whom at least one PK sample post baseline is available will be included in the pharmacokinetic analysis population.

### **8.5.5      Statistical analysis**

A Statistical Analyses Plan will be prepared prior to database lock describing the data analysis in more detail.

#### **8.5.5.1      Demographic and background variables**

Baseline demographic and background variables will be summarized for all subjects. For categorical variables, frequencies and percentages will be provided. For continuous variables, descriptive statistics including the sample size, mean, median, standard deviation and range, will be presented.

#### **8.5.5.2      Subject accountability**

All subjects enrolled will be included in a summary of subject accountability. The frequency and percentage of subjects enrolled in the study, received treatment, discontinued before completing the study, and completing the study will be summarized.

#### **8.5.5.3      Study medication compliance**

A summary of study medication usage and compliance will be provided for all subjects by treatment group.

#### **8.5.5.4      Safety analysis**

- Adverse events (AEs) will be coded and presented using MedDRA. The overall incidence, the incidence of possibly or probably related as well as the incidence of serious adverse events will be summarized per body system in tables. An adverse event that occurred during the study medication period or at follow-up will only be counted as an adverse event if it was either not present at baseline or it was present at baseline but increased in severity during the treatment period.
- Vital Signs (supine blood pressure and heart rate): Descriptive statistics (n, mean, standard deviation, median, minimum, and maximum) will be provided on blood pressure along with heart rate at baseline and all post-dose assessments.
- Hematology, urinalysis and clinical chemistry parameters: Descriptive statistics (n, mean, standard deviation, median, minimum, and maximum) will be provided on values at baseline and all post-dose assessments. Descriptive statistics will be calculated on the change from baseline measurements. Out-of-normal-range values will be indicated for each parameter. The change in out-of-normal-range values after administration and at follow up versus baseline will be summarized by means of shift-tables.
- ECG: Descriptive statistics (frequency, mean, standard deviation, median, minimum, and maximum) on ECG parameters will be provided at baseline and all post-baseline

assessments. Changes from baseline measurements will be calculated and descriptive statistics will be computed. Shift tables will also be provided to indicate changes in ECG parameters over time.

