## **7      Adverse event reporting and follow up**

### **7.1      Definitions**

#### **7.1.1      Adverse event**

Any untoward medical occurrence in a subject or clinical investigation subject, temporally associated with the use of a medicinal product, whether or not considered related to the medicinal product.

Note: An AE can therefore be any unfavorable and unintended sign (including an abnormal laboratory finding), symptom, or disease (new or exacerbated) temporally associated with the use of a medicinal product. For marketed medicinal products, this also includes failure to produce expected benefits (i.e., lack of efficacy), abuse or misuse.

Events meeting the definition of an AE include:

- Exacerbation of a chronic or intermittent pre-existing condition including either an increase in frequency and/or intensity of the condition
- New conditions detected or diagnosed after investigational product administration even though it may have been present prior to the start of the study
- Signs, symptoms, or the clinical sequelae of a suspected interaction
- Signs, symptoms, or the clinical sequelae of a suspected overdose of either investigational product or a concomitant medication (overdose per se will not be reported as an AE/SAE).
- “Lack of efficacy” or “failure of expected pharmacological action” per se will not be reported as an AE or SAE. However, the signs and symptoms and/or clinical sequelae resulting from lack of efficacy will be reported if they fulfil the definition of an AE or SAE.

Events that **do not** meet the definition of an AE include:

- Medical or surgical procedure (e.g., endoscopy, appendectomy); the condition that leads to the procedure is an AE
- Situations where an untoward medical occurrence did not occur (social and/or convenience admission to a hospital)
- Anticipated day-to-day fluctuations of pre-existing disease(s) or condition(s) present or detected at the start of the study that do not worsen
- The disease/disorder being studied, or expected progression, signs, or symptoms of the disease/disorder being studied, unless more severe than expected for the subject's condition.

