### 7.2.1.2 Assessment of Causality

The investigator will make a judgment regarding whether or not, in his/her opinion, the adverse event was related to study agent. The investigator will also evaluate any changes in laboratory values, make a determination as to whether the change is clinically important, and whether or not the changes were related to study drug. However, even if the investigator feels there is no relationship to the study drug, the adverse event or laboratory abnormality must be recorded in the CRF.

Causality criteria are defined as follows:

- **Not related:** the adverse event must definitely be caused by the subject's clinical state, or the study procedure/conditions, or concomitant medication.
- **Remotely/unlikely related:** the study agent is not likely to have any reasonable association with the adverse event.
- **Possibly related:** an adverse event could have been produced by the study agent.
- **Probably related:** the adverse event follows a reasonable temporal sequence from the time of study agent administration, abates upon discontinuation of the study agent and cannot be reasonably explained by the known characteristics of the subject's clinical state.
- **Definitely related:** the adverse event follows a reasonable temporal sequence from the time of study agent administration, abates upon discontinuation of the study agent and reappears when the study agent is introduced.

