### 7.4 Adverse event follow up

If any adverse events considered to be possibly or probably related to study drug are present when the subject completes or is withdrawn from the study, the subject will be re-evaluated until resolution or until the adverse event has stabilized.

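### Drug-related adverse event outputs omit the definitely related grade, and the counting rule read literally skips baseline conditions that first worsen in follow-up

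*Protocol*

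**What the plan says.** **Causality scale (Protocol 7.2.1.2).** There are five grades: not related, remotely/unlikely, possibly, probably and definitely related. For the last, the event must follow dosing in a reasonable time sequence and it "abates upon discontinuation of the study agent and reappears when the study agent is introduced".

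**Related-event listing (Protocol 8.5.1).** "The number and frequency of all adverse events and the adverse events considered possibly or probably related to study will be listed by dose", and then by cumulative dose, body system and coded term.

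**Related-event table (Protocol 8.5.5.4).** Besides the overall incidence, "the incidence of possibly or probably related as well as the incidence of serious adverse events will be summarized".

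**Follow-up of open events (Protocol 7.4).** The duty to re-evaluate uses the same two grades: "If any adverse events considered to be possibly or probably related to study drug are present when the subject completes or is withdrawn".

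**Counting rule (Protocol 8.5.5.4).** For events in the medication period or at follow-up, an event counts only if "it was either not present at baseline or it was present at baseline but increased in severity during the treatment period".

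**What is an adverse event (Protocol 7.1.1).** The definition includes "Exacerbation of a chronic or intermittent pre-existing condition including either an increase in frequency and/or intensity of the condition", with no limit to the treatment period. Section 7.2 has events recorded from consent until 30 days after the end of the study.

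**The concern.** Safety and tolerability at each dose level is a stated objective (Protocol 2). There is no control group (3.1), so the related-event outputs are the main place where a reader sees what the investigators attributed to the drug. A related category that stops at probably related is not monotone: when the evidence strengthens and an event is graded definitely instead of probably related, it leaves the drug-related listing and table.

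The counting rule raises a second, narrower question. Its opening words include follow-up, but its clause on worsening names only the treatment period. The two halves of one sentence therefore treat late worsening of a baseline condition differently from a late new event.

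**Working it through.** The protocol gives no figure for this point, so there is none to reproduce. The check sets the sections side by side and then sizes the effect by simple arithmetic.

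**Step 1. Where each causality grade goes**

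| Grade (7.2.1.2) | All-event listing (8.5.1) and overall incidence (8.5.5.4) | Related listing (8.5.1) | Related table (8.5.5.4) | Re-evaluation at exit (7.4) |
|---|---|---|---|---|
| Not related | yes | no | no | no |
| Remotely/unlikely | yes | no | no | no |
| Possibly | yes | yes | yes | yes |
| Probably | yes | yes | yes | yes |
| Definitely | yes | **no** | **no** | **no** |

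No other section adds the fifth grade to the related category.

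**Step 2. Can the grade occur?** It requires abatement off drug and reappearance on drug. In the extension, Appendix 2 (Tables 9 to 14) alternates eight weeks on drug with four weeks off. Sections 5.6.5.5, 5.6.5.9, 5.6.8.1 and 5.6.8.2 allow a restart after a stop. Section 8.5 gives no separate adverse-event rule for the extension. The grade is therefore not empty by design. Whether weekly dosing in the five-week core treatment also meets the definition is left to the investigator's judgement.

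**Step 3. Size in the related table.** Let n be the number of subjects in a group, x the number with at least one possibly or probably related event, and y the number whose only related events are graded definitely related. The table shows x/n; with all three grades it would show (x + y)/n. The shortfall is y/n. The protocol gives no expected y, so I assume y = 1 and x = 0, and vary n:

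- n = 3 (initial cohort, 3.1): 0/3 shown, 1/3 = 33% with the third grade
- n = 6 (expanded cohort, 3.1): 0/6 shown, 1/6 = 17%
- n = 12 (smallest planned total): 0/12 shown, 1/12 = 8.3%

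If y = 0, the table is unaffected. A subject who also has a possibly or probably related event in the same row is already counted.

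**Step 4. The counting rule, case by case.** The synopsis separates 5 weeks of treatment from 13 weeks of follow-up, and 3.1 also treats them as two periods. The last dose is on day 29 and the last visit on day 120: 120 − 29 = 91 days = 13 weeks.

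| Event | Recorded (7.1.1, 7.2) | Counted (8.5.5.4, literal) |
|---|---|---|
| New, in treatment | yes | yes |
| New, in follow-up | yes | yes |
| Present at baseline, worsens in treatment | yes | yes |
| Present at baseline, first worsens in follow-up | yes | **no** |

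Only the last row is affected.

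**The case against.** The strongest reply is that no event is lost. Definitely related events stay in the all-event listing by dose and in the overall incidence. Serious ones are tabulated, and 7.3 has them followed to resolution or stability whatever their grade. Dose escalation rests on review of all safety data and dose-limiting toxicity (3.1, Table 2), not on the related table. The two-grade phrase is probably shorthand, and an analysis plan due before database lock could group the grades properly. All of this stands, and it limits the point to attribution. It does not remove it: the protocol states the two grades explicitly, and a plan that follows that text inherits the gap.

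On the counting rule, the sentence opens with follow-up in scope, which suggests loose drafting. An exacerbation that starts in follow-up could also be read as a new event under 7.1.1. That reading is possible, so the gap depends on taking the clause literally. It is narrow in any case, because 7.1.1 generally excludes expected progression of the disease itself, and the laboratory shift tables explicitly cover follow-up.

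A reader might infer more from the text than it supports:

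- **That toxicity as a whole is under-reported.** The all-causality outputs contradict this.
- **That injection-site reactions disappear.** Local tolerability is scored separately whatever the causality (5.3.6, Table 5) and is a safety parameter in its own right (8.5.6.2).
- **That follow-up's share of study time (13/18 = 72%) or the drug's long terminal half-life measures the loss.** These describe calendar time and residual drug, not missed events. The 27-day half-life in 1.3.2 comes from a paragraph on monkey studies.
- **That the gap in 7.4 leaves many events unfollowed.** A definitely related event abates off drug by definition, and core-study completion is 13 weeks after the last dose, so few should still be open then.

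**Conclusion.** The point holds in a limited form, at moderate severity. The related-event listing and table contradict the protocol's own causality scale by leaving out its highest grade. The error runs in one direction: the drug-related count is either right or too low. Each subject whose only related events are definite lowers the related incidence by 1/n, which is a third of an initial cohort. That size rests on an assumed single subject; the protocol does not say how often the grade will be used.

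The follow-up clause is an inconsistency within one sentence. Read literally, it leaves uncounted only those baseline conditions that first worsen after treatment. Its numerical effect cannot be derived from the document. Neither defect is shown to change a dose decision.

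**What to change.** 1. In 8.5.1 and 8.5.5.4, define drug-related as possibly, probably or definitely related.
2. In 8.5.5.4, extend the worsening clause from the treatment period to the treatment or follow-up period. It then agrees with the opening of its own sentence and with 7.1.1 and 7.2.
3. Reconcile the two-grade wording of 7.4 with the five-grade scale of 7.2.1.2.

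Items 1 and 2 cost wording changes and re-tabulation of data already collected. Related-event counts stay equal or rise slightly under item 1, and counted events stay equal or rise under item 2. Item 3 may have a small further cost: if the reconciliation brings definitely related events into 7.4, a few re-evaluations could be added.

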## 7.2.1 Evaluation of adverse events

### 7.2.1.1 Intensity/severity grade

The investigator will be asked to assess the severity of the adverse event using the following categories: mild, moderate and severe. This assessment is subjective and the investigator should use medical judgment to compare the reported adverse event to similar type events observed in clinical practice.

Below are listed guidelines for severity assessment:

- **Mild:** Symptom(s) barely noticeable to the subject or does not make the subject uncomfortable. The adverse event does not influence performance or functioning. Prescription drugs are not ordinarily needed for relief of symptom(s).
- **Moderate:** Symptom(s) of a sufficient severity to make the subject uncomfortable. Performance of daily activities is influenced. Treatment of symptom(s) may be needed.
- **Severe:** Symptom(s) of a sufficient severity to cause the subject severe discomfort. Severity may cause cessation of treatment with the study drug. Treatment for symptom(s) may be given.

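### The adverse event counting rule in section 8.5.5.4 leaves out a baseline condition that becomes more frequent at the same severity, although section 7.1.1 defines that as an adverse event

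*Protocol*

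**What the plan says.** Protocol section 7.1.1 lists what meets the definition of an adverse event. The first item is "Exacerbation of a chronic or intermittent pre-existing condition including either an increase in frequency and/or intensity of the condition". Among the things that do not meet the definition it lists "Anticipated day-to-day fluctuations of pre-existing disease(s) or condition(s) present or detected at the start of the study that do not worsen".

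Section 7.2 requires the CRF to hold "Any adverse event experienced by the subject from the time of signing the informed consent until 30 days after the end of the study".

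Section 7.2.1.1 grades severity as mild, moderate or severe. The moderate grade, for example, reads "Symptom(s) of a sufficient severity to make the subject uncomfortable. Performance of daily activities is influenced". Frequency is not a stated criterion for any grade.

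Section 8.5.5.4 says that overall incidence, the incidence of possibly or probably related events and the incidence of serious events will be tabulated per body system. An event during the medication period or follow-up "will only be counted as an adverse event if it was either not present at baseline or it was present at baseline", and in that last case the further condition is that "it was present at baseline but increased in severity during the treatment period".

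Section 8.5.1 separately provides that "The number and frequency of all adverse events and the adverse events considered possibly or probably related to study will be listed by dose", and also by cumulative dose, body system and coded term. It states no baseline filter.

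**The concern.** The definition and the counting rule disagree on what counts as worsening. Section 7.1.1 accepts frequency or intensity; section 8.5.5.4 accepts severity alone, and the word *only* in that rule closes any other route. The investigator must therefore record an event that the analysis must then leave out of the tables.

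This matters because safety and tolerability are a stated objective (section 2), there is no control group (section 3.1), and each subject is his own reference, before against after treatment (section 8.5.1). Change from the pre-treatment state is then the signal of interest, and the rule removes one form of it. Dose groups have 3 to 6 subjects, so a single omitted subject is visible in a percentage. The omission always runs in one direction, towards lower counts.

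The point does not depend on the statistical analysis plan. The protocol itself fixes the counting rule, and a plan that followed 7.1.1 would depart from 8.5.5.4.

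**Working it through.** The protocol gives no figure on this point, so there is nothing to reproduce. The check sets the two sections side by side.

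**Condition present at baseline**

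| Change after dosing | Adverse event under 7.1.1? | Counted under 8.5.5.4? |
|---|---|---|
| Higher severity grade during treatment | Yes (intensity) | Yes |
| Higher frequency, same grade | Yes (frequency) | No |
| No worsening | No | No |

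The sections agree on the first and third rows and contradict each other on the second.

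**Can the severity route absorb the second row?** Only in part. If more frequent episodes disturb daily activities enough to move the grade from mild to moderate, the event is counted. If the grade stays the same, section 7.2.1.1 gives nothing by which frequency could register as a severity increase.

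**Can the exclusions in 7.1.1 remove the second row?** No. They exclude fluctuations that do not worsen, and the same section treats higher frequency as an exacerbation.

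**Size.** Inputs: group size 3, expandable to 6 (section 3.1); total sample 12 to 18 (synopsis). The number of affected subjects is not given, so this is an illustration. It assumes that one subject's only event in a body system is of this kind and that the tables count subjects:

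- group of 3: 1/3 = 33% is reported as 0/3 = 0%;
- group of 6: 1/6 = 17% is reported as 0/6 = 0%;
- all subjects: the incidence falls by 1/12 = 8.3 percentage points with 12 subjects, or 1/18 = 5.6 points with 18.

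If the subject has another counted event in the same body system, his omission does not change that body system's incidence.

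**The case against.** The best reply is that under 7.1.1 the adverse event is the exacerbation, and the exacerbation was not present at baseline, so it enters as new. The rule's own wording tells against this. A rise in severity is also an exacerbation; if exacerbations counted as new, the clause on severity would have no work to do. That clause makes sense only if the thing present at baseline is the underlying condition.

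Second, the events are not lost. Section 8.5.1 provides for listing all adverse events, the synopsis has all safety data listed and summarized, escalation under section 3.1 rests on all safety data collected, and section 8.3 provides for committee review. This stands. It limits the harm to the incidence tables, and a reader should not infer that those tables are the only safety summary.

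Third, the rule might seem to catch more than it does. A reader might infer that it also drops episodes that resolved before dosing and returned at the same grade, or conditions first found after dosing, which 7.1.1 includes: "New conditions detected or diagnosed after investigational product administration even though it may have been present prior to the start of the study". The text does not establish this. Section 3.3.1 and Appendix 2, Table 5 place baseline assessments in the 3 hours before dosing. A condition silent or unknown then can be read as not present at baseline, and so counted. Nor does 7.1.1 name recurrence. What remains is that baseline is not defined for adverse events, which leaves this reading unsecured.

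**Conclusion.** The contradiction on frequency is real and should be corrected. A baseline condition recorded as an adverse event because it became more frequent, at the same grade, is excluded from the overall, related and serious incidence tables. The direction is certain; the size is not, because the protocol says nothing about how often this will occur. The 33% and 17% figures are what one affected subject contributes in a group of 3 or 6, under the assumptions stated with them.

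Two stronger conclusions might be drawn and are not supported. One is that drug toxicity in general is under-counted: not every omitted event would be drug-related, and events new after dosing are counted. The other is that any term reported before dosing is shut out of the counts for the whole of the treatment beyond study. That would need a rule working on coded terms, whereas the protocol's rule asks whether the event was present at baseline.

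**What to change.** In section 8.5.5.4, replace the second half of the counting rule with wording such as: *or the condition was present at baseline and became more severe or more frequent after the first dose (an exacerbation as defined in section 7.1.1).* Any exacerbation that the investigator records under 7.1.1 after the first dose is then counted.

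Add one definition: *present at baseline means ongoing at the assessment before the first dose; episodes that start, recur or are first detected after the first dose are counted as new.* Fluctuations that do not worsen stay out, because 7.1.1 already keeps them from being adverse events.

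The cost is a sentence of analysis text and slightly higher reported incidences. The change relies on the investigator's judgement of exacerbation, so no episode frequency has to be derived from the data. The protocol does not describe the fields of the adverse event page; confirm that it shows whether a recorded event began or worsened after the first dose.
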